#### Sample size calculation

Mixed model analyses will be applied with three measurements comparing two groups (MBCT vs. ETAU, CRT vs. ETAU). There are no previous studies with MS patients that investigated the effect of CRT or MBCT on the primary outcome measure, the Cognitive Failure Questionnaire (CFQ) [23]. Based on a previous RCT using a comparable outcome measure, a medium effect size can be expected [24, 25]. With an alpha of .05, a power of .80, an intra-class correlation of .06, and 33 participants per group, a minimal difference of 0.62 SD can be detected between two groups. Taking into account drop-out and loss to follow-up, we intend to recruit 40 MS patients per group.

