#### Primary outcome measure

The primary outcome measure is the level of subjective cognitive complaints and is measured with the CFQ [23]. Subjective cognitive complaints in terms of executive function will be measured with the Behaviour Rating Inventory of Executive Function – Adult Version (BRIEF-A) [40]. The BRIEF-A consists of a self- and an informant report version.

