### Randomisation and blinding

Following baseline assessment, participants will be randomly allocated to one of three treatment arms (MBCT, CRT or ETAU). First, the location of the intervention will be determined based on the patient’s living location and preference. For each location, randomisation will be performed in variable blocks of 6 and 9, and with an 1:1:1 allocation ratio. A minimisation program will be used to ensure balance between all groups. Minimisation will be performed on three factors: (1) subjective cognitive function, (2) age and (3) gender. Weighting is equal for each factor. The minimisation program will be constructed before the start of the study by an independent scientific programmer. The randomisation procedure will be performed by a researcher who is not involved in administering any outcome measure. Outcome measurements will be administered by assessors who are blind to treatment assignment, but this blinding is not feasible with regard to participants and therapists. Prior to each post-measurement, participants will be reminded not to disclose their group allocation to the assessor.

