### Statistical analysis

#### Descriptive statistics

Data on demographic and clinical characteristics will be summarised in a table. For adherence and other feasibility indicators, frequencies and percentages will be calculated. Satisfaction with the program will be summarised in qualitative descriptions. Differences between groups (CRT vs. ETAU, MBCT vs. ETAU, CRT vs. MBCT, drop-outs vs. treatment completers) in demographic and clinical characteristics and outcome measurements at baseline are analysed using independent samples t-tests (normally distributed continuous outcome variables), Mann-Whitney U tests (skewed continuous outcome variables) and Pearson’s chi-square tests (categorical outcome variables).

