#### Primary and secondary objectives

To evaluate the effectiveness of the interventions, mixed-model analyses will be performed for the primary and secondary outcome measurements with time (baseline, post-intervention, follow-up) as a within subjects factor and condition (CRT vs. ETAU, MBCT vs. ETAU, and exploratory: CRT vs. MBCT) as a between-subjects factor. These analyses will be performed using an intention-to-treat approach, including all randomised participants regardless of adherence and measurement completion. Secondarily, per-protocol analyses will be performed for further exploration of the intervention effects.

To evaluate the secondary study aims, mediation and moderation analyses [61] will be performed to evaluate whether alterations in functional brain networks play a role in the effect of the interventions. In addition, cross-sectional associations between functional brain networks and cognitive function (subjective and objective) will be analysed using Pearson’s correlation and linear regression analyses. To evaluate whether alterations in secondary study parameters are mediating factors that determine subjective cognitive function, mediation analyses [61] and linear regression analyses will be performed. Finally, logistic and linear regression models will be performed to evaluate which factors determine whether a patient is likely to benefit from one of the therapies.

For all analyses, confounding variables will be inserted, such as age and education. Bonferroni corrections will be applied to correct for multiple comparisons within each objective.

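### The effectiveness model does not commit to the allocation factors or to baseline as a covariate, so the primary test is somewhat conservative and loses power

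*Protocol article*

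**What the plan says.** Under Randomisation and blinding, the location is settled first, and then "For each location, randomisation will be performed in variable blocks of 6 and 9, and with an 1:1:1 allocation ratio". In addition, "Minimisation will be performed on three factors: (1) subjective cognitive function, (2) age and (3) gender". The scale that represents subjective cognitive function in the minimisation is not named.

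Under Primary and secondary objectives, the mixed models have condition as the between-subjects factor and are fitted "with time (baseline, post-intervention, follow-up) as a within subjects factor". The only statement on covariates is "For all analyses, confounding variables will be inserted, such as age and education".

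Under Primary outcome measure, "The primary outcome measure is the level of subjective cognitive complaints and is measured with the CFQ". Under Descriptive statistics, baseline comparisons are planned by t-test, Mann-Whitney and chi-square test: "Differences between groups (CRT vs. ETAU, MBCT vs. ETAU, CRT vs. MBCT, drop-outs vs. treatment completers) in demographic and clinical characteristics".

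**The concern.** Minimisation and randomisation by location force the arms to resemble each other on four factors. If such a factor predicts the outcome, forced balance makes the treatment estimate less variable than an analysis that ignores the factor believes. The reported standard error is then too large, the confidence interval too wide and the test conservative. Of the four factors, the article names only age for the model. Education, its other example, played no part in allocation.

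The factor most likely to matter is subjective cognition, because the primary outcome measures the same thing. It enters only as the first level of the repeated outcome. A time-by-condition contrast then compares changes from baseline. That uses the baseline, but less efficiently than covariate adjustment, and it does not fully credit the balance that minimisation created. What is at stake is precision and power, in a trial planned at 80% power with 33 analysed per group.

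**Working it through.** **Inputs from the article.** Allocation 1:1:1 by location; minimisation on subjective cognition, age and gender; 40 recruited per group (120 in all); alpha .05; detectable difference 0.62 SD; baseline as a level of time.

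**Assumed, because the article gives no value.** Baseline-outcome correlation ρ of .4 to .7; the minimised score is the CFQ.

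**The plan's own figure.** The article states "With an alpha of .05, a power of .80, an intra-class correlation of .06, and 33 participants per group", and that "a minimal difference of 0.62 SD can be detected between two groups". A plain two-sided comparison gives (1.960 + 0.842) × √(2/33) = 0.69 SD, not 0.62. With a correlation of .60, a change score gives 2.802 × √(2 × 0.80/33) = 0.617 SD, and so does the mean of two later measurements. Neither uses .06 as written. The figure was not reproduced, and the present point does not depend on it.

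**Step 1: ceiling by formula.** Take the outcome SD as 1. The model variance of a change score is 2(1 − ρ). If the baseline is perfectly balanced, the variance that actually drives the estimate is 1 − ρ². So

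model SE / true SE = √[2(1 − ρ)/(1 − ρ²)] = √[2/(1 + ρ)],

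actual type I error = 2[1 − Φ(1.96 × ratio)].

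| ρ | SE ratio | Type I error |
|---|---|---|
| .4 | √(2/1.4) = 1.195 | .019 |
| .6 | √(2/1.6) = 1.118 | .028 |
| .7 | √(2/1.7) = 1.085 | .034 |

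Real minimisation balances categories of the score, not the score itself, so the effect should be at or below these values.

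**Step 2: simulation.** 2,500 trials per scenario; 120 patients in three arms; minimisation on dichotomised baseline score, age, gender and location, with the best arm chosen with probability 0.8. Treating location as a minimisation factor is an assumption. Assumed effects were 0.2 to 0.5 SD for gender and location and 0.1 to 0.2 SD for age, the same at each visit. The test was two-sided at .05, with power at 0.62 SD, 40 per arm and no dropout. A is change from baseline, adjusted for age and education. B is the later score, adjusted for baseline, age, education, gender and location.

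| ρ; gender and location effect | A: model / empirical SE | A: type I | A: power | B: model SE | B: type I | B: power |
|---|---|---|---|---|---|---|
| .6; 0.2 | 0.201/0.188 (7% too wide) | .036 | .880 | 0.180 | .049 | .927 |
| .6; 0.5 | 0.201/0.192 (5%) | .038 | .876 | 0.176 | .054 | .932 |
| .4; 0.3 | 0.247/0.227 (9%) | .034 | .712 | 0.205 | .052 | .852 |

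A second simulation of the same design, with ρ from .4 to .7, gave a change-contrast SE about 7-12% too wide and type I error about .03. With baseline and all allocation factors, type I error returned to about .05 and the model SE was 11-18% smaller. The first simulation agrees: 0.180/0.201, 0.176/0.201 and 0.205/0.247 are reductions of 10%, 12% and 17%.

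**Step 3: which factor matters.** With baseline as a covariate plus age and education only, type I error was .050 in all three scenarios. Adding gender and location changed the SE by at most 0.003 (about 3% in the second simulation). In the change contrast, adding them moved the SE by no more than 0.001, because an effect that is constant over visits cancels in a change. The baseline score carries nearly everything.

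**The case against.** The strongest reply is that the sentence gives examples and excludes nothing. Age, one of the minimised factors, is among them, and a full protocol or SAP that is not shown may close the list. That stands. A reader might infer that the analysis leaves out location, gender and subjective cognition, or that the model will be chosen freely after the data are seen. The article supports neither; it simply does not commit.

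Second, baseline CFQ is already in the model as a level of time. That also stands, and it limits the size. A reader might reach for √[1/(1 − R²)] with R² = .36, which gives a 25% overstatement and a type I error of .014. That describes a single later score with baseline wholly ignored and perfectly balanced, which is not the planned model.

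Third, the covariate sentence covers all analyses, including the MEG associations and the predictor models. Those are not randomised comparisons, and confounding is the right word there. This stands too.

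Fourth, a reader might infer that the between-arm baseline tests will select covariates. No section says so.

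These replies do not answer one thing: the allocation design and the stated time structure are both on the page, and the structure as written does not make full use of either the balance or the baseline.

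**Conclusion.** The concern holds in a limited form. The article describes an allocation built on four factors and an effectiveness model that commits to only one of them, with baseline used only as a repeated outcome level. The error is conservative. Nothing here suggests an inflated false-positive rate.

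For the time-by-condition contrast, the size is a standard error about 7-12% too wide and a type I error of about .03 instead of .05, for correlations of .4 to .7. The three tabulated scenarios are slightly milder (5-9%, .034 to .038). Power at 0.62 SD rises from .71-.88 to .85-.93 when baseline and the allocation factors are modelled.

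These figures rest on the assumed correlations and on the CFQ being the minimised score. If another scale was used, such as the MSNQ-P from the inclusion criteria, balance on the CFQ is looser and the miscalibration smaller. The precision gain from covariate adjustment over a change contrast remains, because 1 − ρ² is below 2(1 − ρ) for any ρ below 1. Gender and location contribute little; they belong in the model because allocation used them, not because they will change the result much.

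**What to change.** For CRT vs. ETAU and MBCT vs. ETAU:

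- Model the post-intervention and follow-up scores as the response, with the baseline value of the outcome as a covariate. Baseline must then leave the response levels of time, since it cannot be both response and covariate. Equivalently, keep it as a response and constrain the baseline means to be equal across arms. The constrained form also keeps participants with a baseline score only, which suits the stated intention-to-treat approach.
- Include location, age and gender, and the minimisation score where it differs from the baseline outcome. State which scale the minimisation used. If it is the CFQ, one term serves for the primary outcome.
- Education may stay if fixed in advance. Label any other adjustment as a sensitivity analysis.

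The sentence on confounding variables can remain for the non-randomised association analyses. As a secondary point, replace the significance tests between randomised arms at baseline with descriptive statistics, and keep the comparison of drop-outs with completers.

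The cost is wording and a few degrees of freedom. All the variables are collected or recorded already.

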### Objectives

This study primarily aims to examine the effectiveness of CRT and MBCT on subjectively experienced cognitive problems among MS patients. We hypothesise that both CRT and MBCT positively affect subjective cognitive function compared to enhanced treatment as usual (ETAU). We also expect positive effects on the secondary outcome measures objective cognitive function, functional brain network measures, psychological symptoms, well-being, quality of life and daily life functioning. Additionally, we will evaluate in an exploratory way whether there are differences in intervention effects between CRT and MBCT.

Secondary study objectives are:to explore the role of functional brain network measures (using MEG) in subjective and objective cognitive problems, and to evaluate whether there are differences in functional brain network measures between these types of cognitive problems;to explore the role of functional brain network measures as possible mediators in the effect of the interventions;to evaluate whether alterations in objective cognitive function, functional brain network measures, psychological symptoms, well-being, quality of life and daily life functioning are mediating factors that determine subjective cognitive function;to evaluate which factors determine whether a patient is likely to benefit from one of the therapies, such disease severity, severity of cognitive problems and mood at baseline, or gender.

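### The sample size is powered at alpha .05 per contrast, but the analysis Bonferroni-corrects the two primary contrasts, so if the stated .80 power at 0.62 SD holds, it is about .71 at the threshold that will be used

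*Protocol article*

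**What the plan says.** All of this is in the Protocol article.

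- **Objectives.** Both active arms are hypothesised to beat control under the single primary aim: "We hypothesise that both CRT and MBCT positively affect subjective cognitive function compared to enhanced treatment as usual (ETAU"). The CRT versus MBCT comparison is described there as exploratory.
- **Sample size calculation.** The calculation covers both contrasts with control: "Mixed model analyses will be applied with three measurements comparing two groups (MBCT vs. ETAU, CRT vs. ETAU"). The CFQ is named as the primary outcome measure. The inputs are "With an alpha of .05, a power of .80, an intra-class correlation of .06, and 33 participants per group", and the result is that "a minimal difference of 0.62 SD can be detected between two groups". The target is then raised to 40 per group for attrition. Multiplicity is not mentioned.
- **Statistical analysis, Primary and secondary objectives.** The two contrasts with ETAU are tested in mixed models, with CRT versus MBCT again marked exploratory. The section ends with the rule "Bonferroni corrections will be applied to correct for multiple comparisons within each objective".
- **Primary outcome measure.** The CFQ measures the primary outcome. The BRIEF-A is described under the same heading ("Subjective cognitive complaints in terms of executive function will be measured with the Behaviour Rating Inventory of Executive Function") but is not itself called primary.

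**The concern.** The alpha used for planning is not the alpha used for decision. Two confirmatory contrasts within one objective, under a Bonferroni rule applied within each objective, get .05/2 = .025 each. The sample size section gives each contrast the full .05.

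This is not a detail left to a statistical analysis plan. The article states both rules, and they do not agree. What is at stake is the stated power of the primary comparison: a reader who takes .80 at 0.62 SD from the sample size section is given a property that the design does not have at its own threshold.

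**Working it through.** **Inputs.** Alpha .05, power .80, ICC .06, 33 per group, 0.62 SD, 40 recruited per group (Sample size calculation); two primary contrasts (Objectives); Bonferroni within each objective (Statistical analysis). The article does not say whether the test is one- or two-sided; two-sided is assumed unless noted.

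**1. Can the stated figure be reproduced?** For a plain two-group comparison, SE = sqrt(2/33) = 0.246 SD.
- Power at 0.62 SD, two-sided .05: Phi(0.62/0.246 − 1.960) = Phi(0.558) = .712. The detectable difference at .80 power is 2.802 × 0.246 = 0.69 SD, not 0.62.
- With ICC .06, the detectable difference is 0.42 SD (mean of three measures), 0.50 (mean of two), 0.69 (baseline-adjusted), 0.95 (change score) or 0.79 to 0.86 (therapy-group clustering, 6 to 10 per group). None gives 0.62.
- A figure close to 0.62 appears only with settings that the article does not state: a one-sided .05 test ignoring the ICC (0.61 SD), or an ICC of .60 with a change score or a mean of two measures (0.617 SD).

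The stated .80 is therefore taken as given below, not confirmed. The .712 in this step is the uncorrected power of a plain test. It is close to the result in step 2 only by coincidence.

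**2. Effect of the correction, anchored on the article's own claim.** Power .80 at two-sided .05 fixes the ratio of difference to standard error:
- difference/SE = 1.960 + 0.842 = 2.802

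At alpha .025 the critical value is 2.241:
- power = Phi(2.802 − 2.241) = Phi(0.560) = **.712**
- ratio of detectable differences = (2.241 + 0.842)/2.802 = 1.100
- detectable difference at .80 power = 0.62 × 1.100 = **0.68 SD**

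Checks: a noncentral t with 64 degrees of freedom gives .708. If the .05 was one-sided, power after correction is .701 and the detectable difference 0.70 SD.

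**3. Does the recruitment margin cover it?** To keep .80 power at 0.62 SD:
- evaluable per group = 33 × 1.100² = 40
- recruited per group at the article's own 33/40 retention = 40 × 40/33 = 48.5, so 49
- total = 3 × 49 = 147, against 120 planned

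The 40 evaluable per group equals the planned recruitment, so the margin would be enough only with no attrition at all.

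**The case against.** **The .71 rests on a figure that does not reproduce.** This stands. With the article's ICC of .06 and a two-sided .025 test, power at 0.62 SD runs from about .97 (mean of three measures) through .61 (baseline-adjusted) to .34 (change score), depending on what the ICC refers to. None of these readings agrees with the stated .80 at .05 either. So the .71 is a conditional statement. What does not depend on the ICC, under the normal approximation, is the 10% increase in the detectable difference when alpha goes from .05 to .025.

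**Effective numbers may exceed 33.** This stands in part. The mixed model keeps all randomised participants, including those with incomplete measurements, so someone who misses only the follow-up still contributes. On the same anchoring, power at .025 is .75 with 36 per group and .80 with 40. That narrows the gap but does not reconcile the two sections.

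**Separate comparisons of each arm with control may need no correction.** That is a defensible position, but the article does not take it. Its rule has no exemption.

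**A larger family.** A reader might infer that the exploratory contrast, the BRIEF-A forms or separate time points also count, which would push the threshold and the power lower. The text resists each step: CRT versus MBCT is labelled exploratory, the CFQ is the named primary measure, and time enters the mixed model as a factor without separate tests being specified.

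**Conclusion.** The two sections contradict each other on alpha. Conditional on the stated .80 at 0.62 SD with 33 per group and a two-sided .05 test, per-contrast power under the stated Bonferroni rule is about .71, and the detectable difference is about 0.68 SD. The attrition margin does not make up the loss.

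The point goes no further than that. Testing at .025 is conservative and biases nothing; the error is in the stated planning figure. A reader might also infer that the threshold for the primary claim could be settled after seeing the data. The article does not support that. Listing the members of a Bonferroni family and naming a primary time point are commonly left to the full protocol or statistical analysis plan, and neither is at hand.

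**What to change.** Choose one of two statements in the sample size and analysis sections:

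1. Restate the planning figure at alpha .025: 0.68 SD at .80 power, or about 71% power at 0.62 SD, with 33 per group. Both figures inherit the assumption that the stated .80 is correct, so its derivation (what the ICC refers to, and whether the test is one- or two-sided) should be checked at the same time.
2. State that the two primary CFQ contrasts are each tested at .05 and are exempt from the Bonferroni rule. The planning alpha then stands, but the chance of at least one false primary claim can reach up to 2 × .05 = .10, and the article should say that this is accepted.

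In either case, add one sentence: the primary family is the two CFQ contrasts with ETAU, and the BRIEF-A and the exploratory CRT versus MBCT contrast lie outside it.

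The cost is wording, plus a slightly less favourable stated figure under option 1. Holm or Dunnett in place of Bonferroni would be a design preference, not a correction. If one were adopted, the 0.68 SD and 71% would have to be recalculated, since they are single-step Bonferroni values.

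### Cheap improvement, not an error: Holm's step-down correction would replace single-step Bonferroni at the same familywise error and never with less power

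*Protocol article*

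**What the plan says.** Under Statistical analysis, Primary and secondary objectives, the protocol article states: "Bonferroni corrections will be applied to correct for multiple comparisons within each objective". The method is therefore named, and the objective is the family. The same section defines "condition (CRT vs. ETAU, MBCT vs. ETAU, and exploratory: CRT vs. MBCT) as a between-subjects factor", so two contrasts against ETAU are confirmatory and the head-to-head contrast is exploratory.

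Under Objectives it states: "We hypothesise that both CRT and MBCT positively affect subjective cognitive function", with ETAU as the comparator.

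Under Sample size calculation each contrast is sized on its own: "Mixed model analyses will be applied with three measurements comparing two groups (MBCT vs. ETAU, CRT vs. ETAU"). The inputs are "With an alpha of .05, a power of .80, an intra-class correlation of .06, and 33 participants per group", giving "a minimal difference of 0.62 SD can be detected between two groups".

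**The concern.** Single-step Bonferroni tests each of two contrasts at .05/2 = .025 whatever the other contrast shows. Holm tests the smaller p-value at .025 and, if that is rejected, the other at .05. For a fixed family both procedures keep the familywise error at or below .05 under any dependence, and Holm's rejections always include Bonferroni's.

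The difference shows when more than one null hypothesis is false. The protocol expects exactly that, since both treatments are hypothesised to improve on ETAU. At stake is some power on the primary hypothesis in a trial with modest arms, recoverable without more patients or a higher familywise error.

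**Working it through.** **Inputs from the protocol article.** Alpha .05, power .80, 33 per group and 0.62 SD (Sample size calculation); 1:1:1 allocation (Randomisation and blinding); two confirmatory contrasts (Primary and secondary objectives).

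**Assumptions.** Two-sided tests (sidedness is not stated); a family of exactly the two CFQ contrasts; equal true effects where both treatments work; and a variance factor f, which the article does not give.

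**The plan's own figure.** The detectable difference is (1.960 + 0.842) × √(2/33) × √f.
- f = 1: 0.69 SD.
- Averaging repeated measures with intra-class correlation .06: 0.50 SD (two measures) or 0.42 SD (three).
- Treating .06 as a cluster effect with 3 to 10 per cluster: 0.73 to 0.86 SD.

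None of these gives 0.62, so f cannot be derived from the stated inputs. Solving for it gives f = (0.62/0.69)² ≈ 0.81. I use f = 0.8 as a calibrated assumption and f = 1.0 as the alternative.

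**Power per contrast, f = 0.8.** SE = √(0.8 × 2/33) = 0.220, and 0.62/0.220 = 2.816.
- At .05: Φ(2.816 − 1.960) = .80, the planned value.
- At .025: Φ(2.816 − 2.241) = .717.

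**Correlation.** Two contrasts sharing one arm of equal size have correlation .5.

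**Simulation.** Two million draws per setting. Bonferroni rejects where |z| > 2.241. Holm also rejects where |z| > 1.960 if the other contrast exceeds 2.241.

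| True effects (SD) | f | Each treatment: Bonferroni → Holm | Both: Bonferroni → Holm | At least one: either method |
|---|---|---|---|---|
| 0.62, 0.62 | 0.8 | .717 → .769 | .579 → .683 | .856 |
| 0.62, 0.62 | 1.0 | .610 → .664 | .450 → .559 | .770 |
| 0.5, 0.5 | 0.8 | .512 → .564 | .345 → .450 | .678 |
| 0.5, 0.5 | 1.0 | .416 → .463 | .253 → .348 | .579 |
| 0.62, 0 | 0.8 | .717 → .718 (effective arm) | not applicable | .727 |

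Check on the first row: with equal effects, power per treatment is the mean of the last two quantities. (.856 + .579)/2 = .717 and (.856 + .683)/2 = .769, as simulated.

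**Error control.** With no true effect, the familywise error is .046 for both methods. With one effective treatment, the chance of falsely rejecting the other contrast is .025 under Bonferroni and .041 under Holm, still below .05.

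**What Holm leaves open.** Its first step also tests at .025. At that level the detectable difference is (2.241 + 0.842) × 0.220 = 0.68 SD, not 0.62, and 0.62 SD would need about 40 analysable patients per group instead of 33.

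**The case against.** The strongest reply is that nothing here is wrong. Bonferroni is valid under any dependence, fixed in advance and not contradicted elsewhere. Choosing another valid procedure is a matter of efficiency. That stands, and it is why this is an improvement and not an error.

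Bonferroni also has matching simultaneous intervals: for two contrasts, ordinary 97.5% intervals. Holm has no such simple counterpart, and an ordinary 95% interval can exclude zero for a contrast that Holm does not reject. The trade is real but small here, since the article describes no simultaneous intervals.

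The size above is the favourable case: both treatments work equally well, and the largest gain is for rejecting both. The trial is powered for each contrast separately, where the gain is about 5 points. The count of 33 per arm also ignores that "Taking into account drop-out and loss to follow-up, we intend to recruit 40 MS patients per group" and that the mixed models are to include everyone randomised. With more information per arm, all the power figures rise.

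The family of two is an assumption as well. The family is the objective, the BRIEF-A is listed beside the CFQ under the primary outcome heading, and Objectives mentions the secondary outcomes in the same paragraph as the primary aim. In a larger family Holm still never rejects less, but the figures would differ.

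**Conclusion.** The point holds as an optional, low-cost improvement. For whatever family the plan defines, Holm gives the same familywise guarantee and never less power. Under the stated assumptions the gain at 0.62 SD is about 5 points per treatment and 10 to 11 points for showing both. It is about zero if only one treatment works and nil for at least one rejection. The ranking of the two methods does not depend on the variance factor; the figures do.

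A reader might infer more than the document supports:
- *That naming Bonferroni is a mistake.* It controls the error it is meant to control.
- *That much power is lost on the secondary outcomes.* That depends on how many of them have real effects, which is unknown, and nothing in the article allows it to be calculated.
- *That the families should be split by secondary domain at the same time.* That could loosen error control relative to correction by objective, and the argument for Holm does not justify it.
- *That Holm repairs the mismatch between sizing at .05 and corrected testing.* It recovers about 5 of the 8 points lost per treatment when both work, and essentially none when only one does.

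**What to change.** In Primary and secondary objectives, name Holm (step-down Bonferroni) corrections where the text now names Bonferroni corrections, and keep each objective as the family. Add that ordinary 95% confidence intervals will be reported beside Holm-adjusted p-values, and that the adjusted p-values decide significance where the two disagree.

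Make the change before any unblinded analysis. It is a one-sentence amendment plus the note on intervals, needs no further patients or data, and does not raise the familywise error bound. The cost is giving up simple matching simultaneous intervals. The difference between the alpha used for sizing and the corrected alpha needs separate attention.
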